**Physician Recruitment**

Providers will be contacted by recruitment letter sent via USPS and then by email and/or telephone. A dedicated script will be used to assess eligibility and willingness to participate. Physicians will be randomly selected from lists of approximately 5,000 specialists and 25,000 general pediatricians. Physician privacy and confidentiality will be maintained in accordance with HIPAA regulations.

Informed consent will be obtained by having physicians read the consent and provide their signature and date and time of consent. Once this is obtained, physicians will be considered enrolled into the study.

**Sample Size**

The study is adequately powered to detect differences in the combined diagnosis and treatment score as measured by the CPVs®. A sample size of 75 in each arm (225 total) provides over 80% power to detect an estimated 6-7% difference in scores with alpha=0.05. Due to possible attrition, extra subjects may be enrolled to ensure that at least 225 subjects will be used in the analysis.

**Study Hypotheses**

- 1) Clinical practice, specifically decisions around treatment of individuals with disorders postnatal development including DD, ASD, and ID will vary widely among all physician types. This documentation of variation in practice will demonstrate the need for a new diagnostic service that FirstStepDx PLUS and NextStepDx PLUS would fulfill
- 2) FirstStepDx PLUS and NextStepDx PLUS will improve the quality and appropriateness of care and therapeutic plans, as measured by the number of physicians that correctly act on the results of the assay

**Data Analysis**

Summary statistics will be determined for all variables. Simple cross tabulations will be prepared as part of the data resolution process. The calculation of basic descriptive statistics is used to check distributions and find outliers and out-of-range data. Numerical variables will be characterized in terms of means and standard deviations or by medians and interquartile range for skewed or highly non-normally distributed variables. For hypothesis testing, tests will be conducted at a two-sided  $\alpha = 0.05$ .

With experimental data we can estimate the effect of FirstStepDx PLUS or the sequential testing of FirstStepDx PLUS and NextStepDx PLUS on the primary outcomes comparing treatment and control groups. We will use a difference in difference analysis approach comparing differences between groups before and after intervention. We will control for all potential confounders, including physician-level characteristics, such as age, gender, specialty, years in practice, and practice-level characteristics—multi- versus single specialty practice, rural/urban location, and payor mix.

|                   |                                                                                                                 |                      |
|-------------------|-----------------------------------------------------------------------------------------------------------------|----------------------|
|                   | Clinical Study Protocol                                                                                  |                      |
|                   | Title: Establishing the Clinical Utility (ECU) of First Step Dx PLUS and NextStep Dx PLUS |                      |
| Supersedes: Rev B | Document Number: Rev C                                                                                          |                      |
|                   | Effective Date: 11JUNE14                                                                                        | Page: 9 of 20 |

## 1. BACKGROUND INFORMATION AND RATIONALE

### 1.1 Background Information

Approximately 16% of U.S. individuals have a form of developmental disability (Boyle 2011). Genes are one of the few “clinically validated factors” known to be causal for DD, ASD, and ID. As an example, ASD has been found to be up to 70% genetic in origin (Ronald and Hoekstra 2011).

The American Academies of Pediatrics, Neurology, and Child and Adolescent Psychiatry consider the genetics evaluation part of the comprehensive assessment of individuals with disorders of postnatal development including autism spectrum disorder (ASD) (Shen et al 2010; Michelson et al 2011; Volkmar et al 2014). Due to the added clinical detection rate of chromosomal microarray analysis (CMA) over basic genetic testing technologies (such as standard karyotyping), in 2010, the American College of Medical Genetics recommended CMA as a first-tier diagnostic genetic evaluation (Manning and Hudgins 2010). Lineagen’s diagnostic genetic testing, FirstStepDx PLUS, includes the **most comprehensive, whole-genome CMA** currently available for clinical use. It has a two-fold increase in detection rate for variants that underlie ASD (from 5-7% on typical CMA platforms to 12-14% on FirstStepDx PLUS; Matsunami, et al. 2013) and an overall increase in detection rate (from 15- 20% to over 30%). The increased detection rate and resulting clinical management changes of Lineagen’s FirstStepDx PLUS warrants acceptance as *the* first-tier “standard of care” diagnostic genetic test for individuals with disorders of postnatal development. Any individual with a disorder of postnatal development, including ASD, who is receiving an alternate CMA platform is receiving a scientifically and clinically inferior CMA, with a lower established detection rate compared to FirstStepDx PLUS. In certain cases, when whole-genome CMAs are inconclusive, further diagnostic testing is warranted. Lineagen’s NextStepDx PLUS sequencing-based test outpaces other sequencing-based tests to provide actionable clinical information to the pediatrician and pediatric specialist (Matsunami et al., 2014). The higher detection rate of both FirstStepDx PLUS and NextStepDx PLUS results in an increased ability to identify the underlying genetic diagnosis for the patient. Once a genetic diagnosis is obtained, screening and management of associated life-threatening medical risks (seizures, tumors, renal disease, heart disease), administration of indicated medications and therapies, and avoidance of contraindicated treatments can be implemented (Coulter et al. 2011; Ellison et al. 2012).

Appropriate assessment of new health care interventions or technologies requires information on the clinical utility, economic value, affordability, and public health benefits of these interventions (Phillips et al. 2014; Peabody et al. forthcoming). Clinical utility—demonstrating the usefulness of a test for clinical practice—is now the most significant hurdle facing diagnostic technology companies. Today, without scientific evidence of clinical utility, even the most promising technologies may not be covered and reimbursed by payors. Thus, early identification of a data analysis plan that generates evidence on clinical utility is essential for today’s reimbursement environment and must provide scientifically rigorous estimates of how a test will change clinical practice outcomes for patients and populations.

|                   |                                                                                                                 |                       |
|-------------------|-----------------------------------------------------------------------------------------------------------------|-----------------------|
|                   | Clinical Study Protocol                                                                                  |                       |
|                   | Title: Establishing the Clinical Utility (ECU) of First Step Dx PLUS and NextStep Dx PLUS |                       |
| Supersedes: Rev B | Document Number: Rev C                                                                                          |                       |
|                   | Effective Date: 11JUNE14                                                                                        | Page: 10 of 20 |

## 1.2 Rationale for the Study

Appropriate assessment of new health care interventions or technologies requires information on the clinical utility, economic value, affordability, and public health benefits of these interventions (Phillips et al. 2014; Peabody et al. forthcoming). Clinical utility—demonstrating the usefulness of a test for clinical practice—is now the most significant hurdle facing diagnostic technology companies. Today, without scientific evidence of clinical utility, even the most promising technologies may not be covered and reimbursed by payors. Thus, early identification of a data analysis plan that generates evidence on clinical utility is essential for today’s reimbursement environment and must provide scientifically rigorous estimates of how a test will change clinical practice outcomes for patients and populations.

## 2. STUDY DESIGN

The study is an interventional longitudinal study design of physician practice. 225 specialist and general pediatricians without previous exposure to FirstStepDx PLUS or NextStepDx PLUS will be selected from a nationally representative list of approximately 25,000 board-certified pediatricians and 5,000 specialists. These physicians will be **randomized** into one of three arms: to receive information regarding FirstStepDx PLUS (“Intervention A”), to receive information about FirstStepDx PLUS and NextStepDx PLUS (“Intervention B”) for use in clinical practice, and controls not receiving any intervention.

### 2.1 Intervention

The respective interventions will be administered to those randomized into one of the two intervention arms. The intervention consists of information regarding FirstStepDx PLUS alone (Intervention Group A) or sequential testing of FirstStepDx PLUS and NextStepDx PLUS, (Intervention Group B) which will be offered through emailed materials, a pre-recorded 20-minute webinar, and access to questions of the Principal Investigator of the ECU Study and the Lineagen Genetic Counselor.

Group A: Randomized group of 75 physicians who are FirstStepDx PLUS and NextStepDx PLUS naïve at baseline and receive the intervention of FirstStepDx PLUS alone.

Group B: Randomized group of 75 physicians who are FirstStepDx PLUS and NextStepDx PLUS naïve at baseline and receive the intervention of FirstStepDx PLUS and NextStepDx PLUS.

Group C: Randomized group of 75 physicians who are FirstStepDx PLUS and NextStepDx PLUS naïve at baseline and do not receive the intervention (controls).

### 2.2 Study Instruments

A Physician Questionnaire will be administered to all physicians. This questionnaire will assess physician, patient and practice characteristics. Data gathered from this set of questions will become part of the baseline (pre-intervention) assessment and used for analysis. At the baseline assessment, Clinical Performance and Value (CPVs) Vignettes, a validated tool to

|                   |                                                                                                                 |                       |
|-------------------|-----------------------------------------------------------------------------------------------------------------|-----------------------|
|                   | Clinical Study Protocol                                                                                  |                       |
|                   | Title: Establishing the Clinical Utility (ECU) of First Step Dx PLUS and NextStep Dx PLUS |                       |
| Supersedes: Rev B | Document Number: Rev C                                                                                          |                       |
|                   | Effective Date: 11JUNE14                                                                                        | Page: 11 of 20 |

measure physician performance and behavior will be used (Peabody et al 2004). CPV vignettes have been used to establish clinical utility in the molecular diagnostic space. (Peabody et al 2012)

The CPV® vignettes used in this study will simulate a clinical encounter for a patient with an atypical clinical presentation indicative of a possible genetic developmental disorder. Each physician will provide open-ended responses regarding clinical care. These responses are scored in five domains (taking a medical history, performing a physical examination, ordering appropriate tests, making a diagnosis and prescribing treatment against explicit evidence and criteria as determined by the literature and by expert physicians. Results are presented as percentage correct controlling for primacy effects using case within pair randomization. Each case will take approximately 15-20 minutes to complete. All case responses will be completed electronically online and confidential. No physician or practice names are used when reporting the results of the study.

Round 2 of data collection, or post-intervention assessment, will occur 4 weeks after the introduction of the intervention.

CPV scores will be used to compare baseline practice with practice post-intervention in the 3 different physician groups/arms.

This study will test the following hypotheses:

1. Clinical practice, specifically decisions around treatment of individuals with disorders of postnatal development including DD, ASD, and ID will vary widely among all physician types. This documentation of variation in practice will demonstrate the need for a new diagnostic service that FirstStepDx PLUS and NextStepDx PLUS would fulfill.
2. FirstStepDx PLUS and NextStepDx PLUS will improve the quality and appropriateness of care and therapeutic plans, as measured by the number of physicians that correctly act on the results of the assay.

This hypothesis will be tested through total of 9 CPVs consisting of 3 CPVs cases for each of 3 case archetypes as follows.

- Case A: Patients who are currently undiagnosed and for whom FirstStepDx PLUS or would initiate appropriate therapy
- Case B: Patients who are wrongly—or incompletely—diagnosed and for whom FirstStepDx PLUS would change therapy (i.e., terminate inappropriate or unnecessary therapy and initiate appropriate therapy)
- Case C: Patients who are undiagnosed by FirstStepDx PLUS testing and for whom NextStepDx PLUS testing would initiate appropriate therapy and/or earlier intervention will result in better outcomes

The CPVs™ will be randomly assigned to physicians for each to complete 3 CPVs™ (one from each type). Each of the CPVs™ will be scored by physicians for changes in clinical practice including treatment changes, frequency of follow up, laboratory tests and imaging studies ordered - see for scoring sheet.

|                   |                                                                                                                 |                       |
|-------------------|-----------------------------------------------------------------------------------------------------------------|-----------------------|
|                   | Clinical Study Protocol                                                                                  |                       |
|                   | Title: Establishing the Clinical Utility (ECU) of First Step Dx PLUS and NextStep Dx PLUS |                       |
| Supersedes: Rev B | Document Number: Rev C                                                                                          |                       |
|                   | Effective Date: 11JUNE14                                                                                        | Page: 12 of 20 |

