**Study Design** The study uses a randomized controlled study design of pediatric neurologists and developmental pediatricians and front-line (primary care) pediatricians. Physicians will be randomly assigned to a control or one of two intervention arms.

- Pre-intervention/baseline assessment: will be done using pediatric CPV® vignettes and a physician questionnaire to both control and intervention arms.
- Intervention: 2-4 weeks after baseline introduce FirstStepDx PLUS and NextStepDx PLUS to the intervention group of doctors using a webinar format to describe the application and utilization of the two assays.

|                   |                                                                                                                 |                      |
|-------------------|-----------------------------------------------------------------------------------------------------------------|----------------------|
|                   | Clinical Study Protocol                                                                                  |                      |
|                   | Title: Establishing the Clinical Utility (ECU) of First Step Dx PLUS and NextStep Dx PLUS |                      |
| Supersedes: Rev B | Document Number: Rev C                                                                                          |                      |
|                   | Effective Date: 11JUNE14                                                                                        | Page: 7 of 20 |

Post-intervention: 4 weeks post-intervention, a second round of pediatric CPV® vignettes will be administered to both control and intervention arms. FirstStepDx PLUS results will be available to order as part of the vignettes and results will be presented as a downloadable PDF for intervention group 1; FirstStepDx PLUS and NextStepDx PLUS will be available for physicians in intervention group 2.

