#### *Baseline Data Analysis*

At baseline non-parametric estimates of differences will be calculated between the two groups (the control versus intervention groups to examine differences in CPV score and variance and utilization rates). Differences will be adjusted using multivariate and logistic regression models constructed to include age, gender, type of location (urban/suburban vs. rural), patients seen per week, practice size, single or multispecialty practice, practice ownership, and other practice characteristics and by patient characteristics such as type of payers, and use of biologics. Non-parametric estimates of differences in care utilization will be calculated and adjusted for physician, practice and patient characteristics described above.

Summary tables for each group will be generated for the following:

- Percent male
- Percent in single specialty practice
- Percent affiliated with an academic appointment
- Practice location
- Practice size (small, medium or large)
- Average days of week in practice
  - 1 to 2 days
  - 3 to 4 days
  - 5+ days
- Percent practices owned by
  - Physician group
  - Hospital
  - HMO
  - Community health center
  - Other
- Percent of patients covered by
  - Medicare
  - Commercial/Private
  - Medicaid
  - Self-pay / Uninsured
  - Other
- Mean (+/- 2 SD)
  - Years since fellowship
  - Number of patients with DD/ID seen per week
  - Age

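### Hypothesis 1 infers a need for the assays from spread in practice, which cannot show it, and the raw spread of scores also contains case difficulty and scoring noise

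*Protocol*

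**What the plan says.** Hypothesis 1 appears in the Study Synopsis (Study Hypotheses) and again in Protocol Section 2.2. It holds that treatment decisions "will vary widely among all physician types" and then draws the conclusion: "This documentation of variation in practice will demonstrate the need for a new diagnostic service". Section 2.2 presents it as one of the hypotheses that the study will test. Neither place gives a statistic, threshold or reference value for wide variation.

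The assays enter after baseline. The synopsis schedules the intervention with the words "2-4 weeks after baseline introduce", and only for the post-intervention round, in the two intervention groups, does it say that "PLUS results will be available to order as part of the vignettes". Section 2.1 describes all three groups as naïve to both assays at baseline.

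The case pool in Section 2.2 is a "total of 9 CPVs consisting of 3 CPVs cases for each of 3 case archetypes", and these "will be randomly assigned to physicians for each to complete 3 CPVs", one of each type.

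Section 8.2 (Baseline Data Analysis) compares control and intervention groups "to examine differences in CPV score and variance and utilization rates". The adjustment lists and regression models in Section 8.2 contain physician, practice and patient characteristics. None has a vignette term, and the stated mean model has no physician random effect. No primary or secondary endpoint measures spread.

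**The concern.** Two separate problems arise.

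- **The inference.** A finding that physicians differ is treated as proof that they need these particular products. With no criterion for wide variation, almost any data would allow that conclusion to be drawn.
- **The measurement.** Physicians are scored on different cases. Two who practise alike can score differently because one drew harder vignettes, and a three-case mean carries case-to-case noise as well. Raw spread in physician scores is therefore not the same as spread in practice.

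Variability is not a side issue here. The synopsis objective includes reduced variability in practice, and Section 3 makes the effect of testing on variability the objective. Section 1.2 says the evidence is meant to inform reimbursement. A payor's reviewer could readily discount a hypothesis whose conclusion does not depend on the result.

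**Working it through.** **Step 1: the inference, which needs no numbers.** Hypothesis 1 concerns practice among physicians who have never used the assays. To conclude that the assays are needed, one must know that their absence causes the variation or that their presence would reduce it. Both require a comparison of physicians with and without the assays. The protocol has such a comparison: the time-by-intervention interaction in Section 8.2 (Longitudinal Data Analysis), under randomisation. Hypothesis 1 does not use it.

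**Step 2: what the protocol reveals about SDs.** Its only computed figure is over 80% power with 75 per arm for a 6-7% difference at two-sided 0.05. Solving for the SD of the quantity compared:

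SD = d / [(1.960 + 0.842) × sqrt(2/75)]

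This gives at most 13.1 for d = 6 and 15.3 for d = 7. The power claim is attainable but cannot be verified, and it says nothing about how the SD divides between physicians, cases and residual.

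**Step 3: overlap of cases.** With one of three cases from each of three archetypes there are 3 × 3 × 3 = 27 sets. If cases are drawn independently, two physicians share all three with probability 1/27 (3.7%) and none with probability (2/3)³ = 8/27 (29.6%).

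**Step 4: size of the effect on spread.** For a three-case mean,

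Var = s²(physician) + s²(case)/3 + s²(residual)/3,

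where the case SD is within archetype, because every physician gets one case of each type. The spread among physicians on the same vignette is sqrt[s²(physician) + s²(residual)]. The SDs below are assumptions, in score points. Differences are taken before rounding.

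| Assumed SDs (physician, case, residual) | SD of three-case mean | Same, no case term | Added by case draw | Excess over physician SD | Within-vignette SD |
|---|---|---|---|---|---|
| 10, 5, 10 | sqrt(100 + 25/3 + 100/3) = 11.9 | sqrt(100 + 100/3) = 11.5 | 0.4 | 19% | sqrt(100 + 100) = 14.1 |
| 8, 6, 12 | sqrt(64 + 36/3 + 144/3) = 11.1 | sqrt(64 + 144/3) = 10.6 | 0.6 | 39% | sqrt(64 + 144) = 14.4 |
| 5, 10, 15 | sqrt(25 + 100/3 + 225/3) = 11.5 | sqrt(25 + 225/3) = 10.0 | 1.5 | 131% | sqrt(25 + 225) = 15.8 |

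Most of the excess over the physician SD comes from the residual and little from the random draw of cases.

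**Step 5: no physician main effect at all.** With case SD 5 and residual SD 10, the formula gives sqrt(25/3 + 100/3) = 6.5. For (10, 10) it gives 8.2 and for (10, 15) it gives 10.4. A simulation of 225 physicians, with three cases per archetype drawn from a wider pool, gave 6.2, 7.4 and 9.8. It is lower because three sampled cases have on average two thirds of the pool's variance. A visible spread of scores therefore does not by itself show that some physicians perform consistently better than others.

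**The case against.** The strongest reply is that little depends on Hypothesis 1. No endpoint or decision rule is tied to it, assay benefit is the subject of Hypothesis 2, and the primary predictor is already the randomised interaction. It is also natural to describe need before a product is introduced. That is fair as to consequence. But the protocol lists the statement as a hypothesis under test and writes its conclusion in advance, and no later analysis document can make that conclusion follow.

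On measurement, several points stand:

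- Hypothesis 1 does not mention baseline. That reading comes from its pre-assay logic and from the baseline analysis of variance.
- That analysis compares arms, and random assignment of vignettes does not bias it.
- One case per archetype removes difficulty differences between archetypes.
- A vignette effect could be added in a statistical analysis plan that is not at hand. That would answer the measurement point but not the inference.
- With one response per physician per case, the residual includes different physicians handling the same patient differently. This is arguably practice variation in the sense of Hypothesis 1, and the within-vignette SDs of 14.1 to 15.8 exceed the score SDs of 11.1 to 11.9. Counting only the physician main effect could understate variation.

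A reader might infer that the design manufactures most of the spread, or that reported variation would be inflated by 19% to 131%. The documents support neither: the SDs are assumed, the case draw contributes the small part, and the residual cannot be split into noise and real practice differences.

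**Conclusion.** The point holds on two legs of unequal weight. The main one is logical: documented variation among physicians naïve to the assays, judged against no criterion, cannot demonstrate a need for them. This rests only on the protocol's text.

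The second is that raw spread of physician scores contains within-archetype case difficulty and scoring noise, which no stated model separates out. Its size cannot be fixed from the protocol. Under the assumed SDs the case draw accounts for about 0.4 to 1.5 points.

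A reader might also infer that the primary result is compromised. It is not: vignettes are assigned at random, so case difficulty is independent of arm and does not bias the randomised comparison. What changes is the claim that may be drawn from Hypothesis 1. The sponsor should correct it.

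**What to change.** - **Study Synopsis (Study Hypotheses) and Section 2.2:** delete the sentence on demonstrating need, so that Hypothesis 1 becomes descriptive, and rest any claim about the assays on the between-arm contrast.
- **Section 8.2:** describe variation from vignette-level scores with vignette as a fixed effect and physician as a random effect. Report both the between-physician SD and the within-vignette SD (physician plus residual), each with an interval, and say that the residual may mix real physician-by-case differences with noise.

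If three vignettes are completed at baseline and assignment is balanced, this uses 225 × 3 = 675 scores, or 675/9 = 75 per vignette. The protocol states neither condition explicitly.

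The cost is wording and a small extra analysis, provided that vignette-level scores and vignette identities are kept. The claim drawn from Hypothesis 1 becomes more modest.

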## Outcome Measures

### Primary Outcome

- Difference in combined diagnostic and treatment CPV® domain score post-intervention versus baseline comparing intervention and control groups

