## 6. STUDY PROCEDURES

At enrollment, each eligible physician who agrees to participate will be assigned a unique subject identification number to be applied on all forms. Only the study team will have access to the subject's identity. The subject's name or other identifying information will not be used in analysis or reporting.

The main study procedures or assessments will include but are not limited to: collection of demographic and practice information during the screening process and completion of CPVs.

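### The rule that physicians score each vignette for changes in practice leaves side-by-side rating of rounds open, and nothing masks scorers to arm or round

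*Protocol*

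**What the plan says.** The primary outcome in the Synopsis is the "Difference in combined diagnostic and treatment CPV" domain score, post-intervention versus baseline, compared between intervention and control groups. The score comes from free text: Section 2.2 states "Each physician will provide open-ended responses regarding clinical care".

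Section 2.2 describes the scoring twice:

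- The responses are scored in five domains "against explicit evidence and criteria as determined by the literature and by expert physicians", and results are given as percentage correct.
- Later in the same section, each vignette "will be scored by physicians for changes in clinical practice including treatment changes, frequency of follow up, laboratory tests and imaging studies ordered", with a pointer to a scoring sheet.

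The model in Section 8.2 takes a score for each physician at each time. It reads the effect from the time-by-intervention interaction.

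On what the scorers will see, the Synopsis (Study Design) says that in Round 2 the FirstStep "results will be available to order as part of the vignettes and results will be presented as a downloadable PDF for intervention group 1", and that FirstStep and NextStep "PLUS will be available for physicians in intervention group 2". Controls are offered neither.

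On coding, Section 6 says that each physician "will be assigned a unique subject identification number to be applied on all forms" and "Only the study team will have access to the subject's identity". The protocol does not mention masking of scorers, duplicate scoring or adjudication.

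**The concern.** Three features come together. People rate the primary outcome by matching free text to criteria, which leaves some room for judgement. One of the two scoring instructions, taken literally, needs an earlier round to compare with. And the content that can identify an arm appears mainly where bias would do most harm, in Round 2 answers from the intervention arms.

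The estimand is the differential change over time. A scorer who is more generous to recognisable intervention answers in Round 2 adds that generosity directly to the TIME x INTERV coefficient. Randomisation, covariate adjustment and differencing against baseline do not remove it, because it arises after allocation and is confined to one arm and one round.

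The physician ID does not help here. It protects identity; it does not hide arm or round, and the protocol does not say whether scorers belong to the study team that holds the identities.

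**Working it through.** **1. The two scoring descriptions compared.**

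| Place | What is rated | Where change comes from |
|---|---|---|
| Section 2.2, first description | Each response, percentage correct against explicit criteria | Not part of scoring |
| Section 2.2, second description | Each vignette, for changes in practice | Can be read as part of scoring |
| Section 8.2, model | One score per physician per time | TIME x INTERV |

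The first and third rows agree. The second agrees with them only if it is read as a list of scoring-sheet items.

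**2. Which scorer errors matter.** Let b be the average extra credit in a group and round. The difference in difference is (intervention post − intervention pre) − (control post − control pre).

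- If scorers know the round and drift by b in Round 2 in all arms, the error is b − b = 0.
- If they drift by b only in intervention Round 2, the error is b.

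Only drift that differs by arm counts. Here b is the arm average, so leniency on recognised vignettes must be multiplied by the share that is recognised.

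**3. The SD implied by the plan's power statement.** Section 8.1 gives 75 per arm, over 80% power, a 6-7% difference and alpha 0.05 (two-sided, Section 8.2). It gives no SD, so the power cannot be reproduced. The largest SD consistent with 80% power is d / [(1.960 + 0.842) x sqrt(2/75)]:

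- d = 6: 6 / (2.802 x 0.1633) = 13.1
- d = 7: 7 / (2.802 x 0.1633) = 15.3

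SDs of 13 and 15 therefore lie near the upper limit of what the plan's own claim allows.

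**4. Type I error under an assumed drift.** The drift of 1 or 2 points is an assumption; the documents give no figure for scorer error. For a post-only comparison, SE = SD x sqrt(2/75), and with no true effect the rejection probability is P(|Z + b/SE| > 1.96).

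| SD | SE | b = 1 | b = 2 |
|---|---|---|---|
| 13 | 2.12 | 7.6% | 15.6% |
| 15 | 2.45 | 6.9% | 12.9% |

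Against the target difference, 1/7 = 14% and 2/6 = 33%.

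**5. The same calculation for the interaction.** Let r be the correlation between a physician's scores before and after, with equal SDs. Then SE = SD x sqrt(2(1 − r)) x sqrt(2/75). The protocol does not state r. At SD 13:

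| r | SE | b = 1 | b = 2 |
|---|---|---|---|
| 0 | 3.00 | 6.3% | 10.2% |
| 0.5 | 2.12 | 7.6% | 15.6% |
| 0.7 | 1.64 | 9.3% | 22.9% |

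The post-only figures equal the interaction figures only at r = 0.5.

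**The case against.** A reader might infer that the scorers do work with knowledge of arm and round. The protocol does not say so. Section 2.2 also uses the idea of change within a single case: in archetype B the test result would alter that patient's therapy, which can be marked from one vignette. The same section compares rounds by means of scores, which implies that scoring comes first, and Section 8.2 models a score at each time. The phrase may do no more than list items on the scoring sheet, several of which (laboratory tests, imaging) belong to secondary utilization outcomes. This objection stands: the wording is ambiguous, and unmasked scoring is not shown.

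Four further points stand in part.

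- Explicit criteria limit discretion, so the outcome depends on judgement at the margin and is not a global subjective rating.
- An assay name is not a perfect marker of arm. Only prior use is an exclusion (Section 4.1.2) and awareness is a covariate (Section 8.2), so a control physician could name an assay, and an intervention physician might order none.
- The scoring sheet is not in the text at hand. Nothing supports an inference that it credits a diagnosis differently according to the test that led to it.
- The drift and SD are assumed, so the percentages illustrate sensitivity and do not measure a defect.

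None of this supplies masking, or rules out side-by-side rating by someone who follows the sentence as written. Nor is it a detail to leave to an analysis plan: who rates the primary outcome, and what they see, is study conduct, and the protocol itself sets the rule.

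**Conclusion.** The point holds as a weakness in how scoring is specified. The rule permits unmasked, side-by-side rating of a primary outcome that depends partly on judgement, and Round 2 content can reveal the arm. Whether bias would follow, and of what size, cannot be established from the document.

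The quoted range of about 7-16% rests on three assumptions: an average arm-specific drift of 1 to 2 points, an SD of 13 to 15, and a post-only comparison. For the interaction itself, the SD 13 figures alone run from 6.3% to 22.9% as r goes from 0 to 0.7. The change is worth making because it is cheap and removes the ambiguity.

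**What to change.** Replace the sentence in Section 2.2 with a rule along these lines:

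- The existing scorers score each vignette once, on its own, against the explicit checklist.
- Vignettes are presented in random order across arms and rounds, with physician ID, arm and round labels removed.
- Change is computed from the scores and is not rated.
- For the diagnosis and treatment domains only, assay brand names are replaced by a neutral term where feasible. The original test names stay in place for the test-ordering domain and the utilization endpoints, which need to know which test was ordered.

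**Cost.** The answers are already collected electronically, so this adds a masking and shuffling step and needs no extra scorers or subjects. Keeping test names for some domains means preparing the text in two forms. Masking will be imperfect where an answer describes a report in detail, and scoring has to wait until both rounds can be mixed.
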